## Abstract

**Background:**

In Germany, about 20% of the total population have a migration background. Differences exist between migrants and non-migrants in terms of health care access and utilisation. Colorectal cancer is the second most common malignant tumour in Germany, and incidence, staging and survival chances depend, amongst other things, on ethnicity and lifestyle. The current study investigates whether stage at diagnosis differs between migrants and non-migrants with colorectal cancer in an area of high migration and attempts to identify factors that can explain any differences.

**Methods/Design:**

Data on tumour and migration status will be collected for 1,200 consecutive patients that have received a new, histologically verified diagnosis of colorectal cancer in a high migration area in Germany in the previous three months. The recruitment process is expected to take 16 months and will include gastroenterological private practices and certified centres for intestinal diseases. Descriptive and analytical analysis will be performed: the distribution of variables for migrants versus non-migrants and participants versus non-participants will be analysed using appropriate *χ*2-, t-, F- or Wilcoxon tests. Multivariable, logistic regression models will be performed, with the dependent variable being the dichotomized stage of the tumour (UICC stage I versus more advanced than UICC stage I). Odds ratios and associated 95%-confidence intervals will be calculated. Furthermore, ordered logistic regression models will be estimated, with the exact stage of the tumour at diagnosis as the dependent variable. Predictors used in the ordered logistic regression will be patient characteristics that are specific to migrants as well as patient characteristics that are not. Interaction models will be estimated in order to investigate whether the effects of patient characteristics on stage of tumour at the time of the initial diagnosis is different in migrants, compared to non-migrants.

**Discussion:**

An association of migration status or other socioeconomic variables with stage at diagnosis of colorectal cancer would be an important finding with respect to equal health care access among migrants. It would point to access barriers or different symptom appraisal and, in the long term, could contribute to the development of new health care concepts for migrants.

**Trial registration:**

German Clinical Trials Register DRKS00005056.

## Background

Around 16 million people with a so-called migration background currently live in the Federal Republic of Germany [1], corresponding to almost 20% of the total population. This includes foreign nationals, but also naturalised migrants and those born in Germany with at least one parent who migrated (all referred to as migrants in the text) [2]. Migrants have entered Germany since World War II, including late-migrants from the collapsing Union of Soviet Socialist Republics, immigrating labourers (mainly from Turkey, Greece, Italy and Spain), and also fugitives or asylum-seekers from very different countries in the world.

In addition to integration through language, work and social life, access to appropriate health care is essential for migrants. With the National Integration Plan, the Federal Government has enshrined such integration in its politics [3]. Compared to the rest of the population, migrants are often worse off from a social perspective [4]. Educational background, as well as a person’s living and working situation all influence the risk of illness, and in turn health problems have a detrimental effect on educational and job opportunities [4]. Differences also exist between migrants and non-migrants in terms of health care. Migrants take advantage of prevention and early detection programmes less often than non-migrants and consult doctors less frequently [5]. This may be because some migrant populations are less familiar with the concept of routine screening to detect health problems before the onset of symptoms [6,7].

Studies from other countries report that incidence, stage and survival chances depend, amongst other things, on ethnicity [7-10]. A recent epidemiological review reports that age-standardised mortality and the incidence of gastrointestinal tumours are lower among migrants [11]. This may be partially attributable to selection effects: lower average age, lower exposure to colorectal cancer (CRC) risk factors (‘Mediterranean diet’, less alcohol), the ‘healthy migrant effect’ etc. Nevertheless, tumours are among the leading causes of death among migrants [11].

There are more than 65,000 new cases of and 25,000 deaths from CRC in Germany per year, making it the second most common malignant tumour [12]. The cumulative lifetime risk of developing CRC is 6.1% for women and 7.5% for men [12]. Median age at diagnosis is 71 years for men and 75 years for women [12], and many first generation migrants in Germany are now entering this age range.

As the CRC survival rate depends on the stage of the tumour at diagnosis [13,14], and late-stage CRC diagnoses result in higher health costs [15,16], early detection is important. It is therefore necessary to examine whether migrants are generally diagnosed at a similar stage of CRC and, apart from migration status, what further predictors of late-stage CRC should be taken into account.

To the best of our knowledge this is the first study to be conducted in Germany that examines whether CRC stage at diagnosis differs between migrants and non-migrants in an area of high migration (metropolitan area of Frankfurt am Main / Hanau / Offenbach, Germany). Furthermore, we will study possible explanatory factors for any differences that occur.

## Methods/Design

### Study design and setting

KoMigra is a cross-sectional, prospective observational study: during a 16-month consecutive recruitment process in the Frankfurt am Main / Hanau / Offenbach metropolitan area, data on tumour and migration status will be collected for 1,200 patients that have been newly diagnosed with CRC. Details on methods and design are laid down in the original study protocol, which can be requested from the corresponding author.

### Main and auxiliary questions

Is there a difference in the distribution of CRC tumour stage (based on the UICC (Union Internationale Contre le Cancer) classification) at diagnosis between migrants and non-migrants? What factors may explain any differences?

### Sample size calculation

The net sample size was fixed at 1,047 patients. The proportion of migrants in the study area is substantially higher than for Germany as a whole. The share is 43% for Frankfurt [17], 33% for Hanau and 55% for Offenbach [18]. However, migrants in Germany tend to belong to younger age groups: in Frankfurt, only 15.6% of the population aged 65 and over has a migration background [19]. According to the Schleswig-Holstein cancer register, the share of CRC patients in UICC stage I was 17% [20]. Assuming this share is only half as high among migrants (17% in the German population, compared with 8.7% for migrants), this difference can be detected with a significance level of ≤ 5% and a statistical power of 80%. To allow for possible losses, we plan the recruitment of 15% more patients and thus achieve a final sample size of 1,200.

### Sampling and recruitment, study timeline

In order to collect data from all persons that have been diagnosed with CRC independently of their origin and stage of disease, we will ask all providers of colonoscopies (gastroenterological private practices and certified centres for intestinal diseases [21]) in the region of study to participate.

Recruitment centres must conform to the following inclusion criteria: they must be located within a 20 km radius of one of the three city centres. The gastroenterological private practices must be officially permitted to carry out and charge for preventive and/or curative colonoscopies. The centres for intestinal diseases must be certified in accordance with German Cancer Foundation guidelines [21].

Nine certified centres for intestinal diseases and 68 qualified gastro-enterologists in private practice were identified and subsequently invited to participate in the study in an information letter sent out at the beginning of 2013. Starting from August 1, all recruitment centres will be asked for their participation agreement and instructed to initiate patient recruitment. During a 16-month period from August 1, 2013 to November 30, 2014, 1,200 patients with newly diagnosed CRC are expected to be consecutively included in the study. Recruitment centres will receive a compensation of 50 Euro for every CRC patient that is included in the study and whose documentation is complete. A timeline for the study is presented in Figure 1.

**Figure 1 F1:**
[figure not shown]
**Timeline of the KoMigra study.** MS = Milestone.

### Patient in- and exclusion criteria

To satisfy the inclusion criteria, a new and histologically confirmed CRC diagnosis during the previous three months is required, the patient must be resident in Germany and he or she must have provided valid consent to participate in the study. A patient will not be included if he or she has ever been previously diagnosed with another cancer (i.e. CRC is a second tumour; the only exception is basal-cell carcinoma).

### Data collection

At the recruitment centres, details of all CRC patients will be documented in a screening list. It assesses the in- and exclusion criteria of the patient and provides a complete record of all the presenting CRC patients during the recruitment period. If the patient fulfils all of the inclusion and none of the exclusion criteria, the study will be explained and he or she will subsequently be provided with an information sheet and informed consent will be obtained.

For all non-participants, the study personnel will note information on age, gender and tumour stage in the screening list as well as whether language problems were the reason for non-participation. In addition, the physician or health care assistant will provide information on the assumed migration background and country of origin.

The clinical tumour data form assesses details on CRC diagnosis, histomorphology of tumour and stage of disease, as well as patient risk factors (see Additional file 1). The CRC patient will be given a questionnaire with simple questions relating to socio-demographics and migration (see Additional file 2). The questions on the patient’s migration background are based on published methodological standards used in epidemiology research [22,23]. The migration background will be operationalised via the patient’s and his or her parents’ place of birth: Patients born outside Germany will be considered to be first generation migrants, while patients whose mother and/or father was/were born outside Germany will be considered to be second generation migrants.

In addition to the German version, the patient questionnaire, patient information sheet and informed consent will also be available in nine other languages that are common in the study region. The translation of the documents will be entrusted to a certified translation agency that can provide references in the field of clinical research.

All data will be monitored by study personnel during regular monitoring visits. Collected data will be promptly entered into a database at the Institute of General Practice to ensure they are recorded and kept securely. Data will be analysed in pseudonymous form. Before entries are made in the database, each patient will be checked to ensure he or she has not been documented by another centre, thus avoiding the duplication that can, for example, result when a gastroenterologist in private practice refers a patient to a centre for intestinal diseases. Personal data will be stored separately from identification features. Data collection will be concluded on December 31, 2014.

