### Analysis

The statistical evaluation will consist of a descriptive and an analytical section. Categorical characteristics (such as country of birth) will be aggregated appropriately, so that if possible no category includes fewer than 10% of all test persons. In the descriptive section, the distribution of all factors collected from the questionnaires will be presented in two groups according to whether the test person has a migration background or not. The distribution of characteristics collected from non-participants will be described in the same way. Differences in the distribution of migrants versus non-migrants and participants versus non-participants will be compared using appropriate *χ*2-, t-, F- or Wilcoxon tests.

In the analytical section, the same variables will be subjected to explorative analysis by means of multivariable, logistic regression models, with the dependent variable being the dichotomized stage of the tumour (UICC stage I versus more advanced than I). Odds ratios and associated 95%-confidence intervals will be calculated. Furthermore, ordered logistic regression models will be estimated, with the exact stage of the tumour at diagnosis as the dependent variable. Predictors used in the ordered logistic regression will be both patient characteristics that are specific to migrants (how long in Germany, knowledge of German language, etc), as well as patient characteristics that are not specific to migrants (age, gender, socioeconomic status etc.). By including the first type of variable in the regression models, it will be possible to judge whether migration status remains influential in migrants that have been living in Germany for a long time, speak the language well etc. By including the latter type of variable in the regression models, it will be possible to judge whether migration status has an (additional) effect, after adjustment for variables whose distribution among migrants is different to that among non-migrants (socioeconomic status, age, etc.). Interaction models will be estimated in order to investigate whether the effects of patient characteristics on stage of tumour at the time of the initial diagnosis are different in migrants, compared to non-migrants. A detailed description of the statistical methods used in this study will be provided in a Statistical Analysis Plan (SAP) which will be finished before database lock.

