### Avoidance of bias

Participation rates in studies are generally influenced by potential participants’ availability, ability to answer questions and readiness to cooperate. In the case of migrants, the factors ‘availability’ and ‘ability to answer questions’ (e.g. due to insufficient knowledge of German) present the greatest recruitment problems [24]. It is the aim of study recruitment to ensure that suitable measures are taken to counter well-known problems in order to keep selective participation to a minimum [25,26]: the translation of patient-relevant study documents into the nine most commonly spoken languages, as well as the use of simplified and easily comprehensible language in the patient questionnaire are two examples of these. Furthermore, the patient questionnaire should be filled in with the help of either the treating gastroenterologist or the health care assistant in order to enable illiterate and elderly patients, as well as patients with language difficulties to participate. The implementation of such measures aims to minimise any bias that may result from low participation rates among migrants.

In order to avoid systematic bias resulting from different care pathways and to achieve a representative sample with respect to the distribution of CRC tumour stages, CRC patients will be recruited from both gastroenterologists in private practice and certified centres for intestinal diseases throughout the Frankfurt / Hanau / Offenbach region.

Selection bias resulting from the aforementioned variables (e.g., higher participation of patients with low-stage as opposed to high-stage CRC) cannot be ruled out. It can, however, be assessed and described on the basis of the documentation of all participating and non-participating CRC patients in the screening list.

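### Migration background is a staff assumption for non-participants but questionnaire-based for participants, so the check on selective participation by migration status mixes two measures and can hide or invent a difference

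*Protocol article*

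**What the plan says.** The protocol article sets out two sources for the study's exposure, both under Data collection.

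- Non-participants: "For all non-participants, the study personnel will note information on age, gender and tumour stage in the screening list". The same paragraph adds that "the physician or health care assistant will provide information on the assumed migration background and country of origin".
- Participants: "The CRC patient will be given a questionnaire with simple questions relating to socio-demographics and migration". The definition is explicit: "The migration background will be operationalised via the patient’s and his or her parents’ place of birth". It reaches the second generation: "patients whose mother and/or father was/were born outside Germany will be considered to be second generation migrants".

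Two later sections use these data. Analysis states: "Differences in the distribution of migrants versus non-migrants and participants versus non-participants will be compared using appropriate" tests, and it also has the non-participants' characteristics described by migration background, as for participants. Avoidance of bias concedes that selection bias cannot be excluded, then says: "It can, however, be assessed and described on the basis of the documentation of all participating and non-participating CRC patients in the screening list".

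The article does not say that the staff assumption is also recorded for participants, that it is checked against the questionnaire, or that the difference in source limits the comparison.

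**The concern.** The study asks whether migrants are diagnosed at a different stage from non-migrants. Its answer is credible only if participation does not depend on migration status and stage together. The article recognises this and offers the screening list as the means of judging it.

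For migration status, that check compares a questionnaire definition in one group with a staff impression in the other. Staff may miss a German-born patient with one foreign-born parent, who counts as a migrant under the study definition. They may also take someone for a migrant who is not one. Either error enters the non-participant column only. A difference, or the absence of one, can then come from measurement alone.

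Two outputs are weakened: the migrant share in participants against non-participants, and stage by migration status among non-participants. The second bears most directly on whether selection could distort the main result.

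**Working it through.** **Inputs.** From Sample size calculation: a migrant share of 15.6% (Frankfurt residents aged 65 and over) and stage I shares of 17% and 8.7%. Se and Sp of the staff assumption against the questionnaire definition, and the number of non-participants, are not in the article. The values below are assumptions.

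**The plan's own figure.** The article does not state which migrant share lies behind the net size of 1,047, so I checked 15.6%. With k = 0.156/0.844 = 0.185, two-sided 5%, 80% power and the pooled-variance formula for two proportions, the requirement is 866 + 161 = 1,027, within 3% of 1,047. Power at 1,047 is 80.9%. So 15.6% is a reasonable planning share to use here. The point does not rest on the sample size and changes nothing in it.

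**Share shown among non-participants.** For a true share π:

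shown share = Se × π + (1 − Sp) × (1 − π)

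The true share that would be shown as 15.6% is q = [0.156 − (1 − Sp)] / (Se + Sp − 1).

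| Se | Sp | Shown, if truly 15.6% | True share shown as 15.6% |
|---|---|---|---|
| 0.6 | 1.00 | 9.4% | 26.0% |
| 0.7 | 1.00 | 10.9% | 22.3% |
| 0.8 | 1.00 | 12.5% | 19.5% |
| 0.9 | 1.00 | 14.0% | 17.3% |
| 0.9 | 0.98 | 15.7% | 15.5% |
| 0.9 | 0.95 | 18.3% | 12.5% |

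Example, last row: 0.9 × 0.156 + 0.05 × 0.844 = 0.140 + 0.042 = 0.183.

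**Invented difference.** Suppose 1,200 participants and 600 non-participants, both truly at 15.6%. With Sp 1 and Se 0.9, 0.8, 0.7 and 0.6, a 5% test reports a difference with probability about 14%, 42%, 78% and 97%. With 300 non-participants the figures are about 9%, 26%, 54% and 82%.

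**Hidden difference.** Take Se 0.6, Sp 1 and 600 non-participants, of whom 26.0% (156) are truly migrants. Participants include 0.156 × 1,200 = 187 migrants. True participation is 187/(187 + 156) = 55% in migrants and 1,013/(1,013 + 444) = 70% in non-migrants, yet the comparison shows 15.6% against 15.6%.

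**Stage by migration status in non-participants.** Assume the planning stage I shares (17% and 8.7%, 8.3 points apart) hold among them and that staff error is unrelated to stage. With Se 0.9 and Sp 0.95:

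- assumed migrants: (0.1404 × 0.087 + 0.0422 × 0.17)/0.1826 = 10.6%
- assumed non-migrants: (0.8018 × 0.17 + 0.0156 × 0.087)/0.8174 = 16.8%

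The gap shrinks to 6.2 points without any selection.

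**With a common measure.** If the staff assumption is recorded in both groups with equal error rates, shown difference = (Se + Sp − 1) × true difference. Equal true shares then look equal. In the hidden case above, participants would show 0.6 × 15.6% = 9.4% against 15.6% in non-participants. The difference is reduced from 10.4 to 6.2 points, but it is visible.

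**The case against.** People who decline cannot be made to complete a questionnaire, so a proxy is unavoidable, and the article openly labels it as assumed. This stands, and it is why the remedy is a common measure rather than better data on decliners.

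The article is condensed, and the screening-list form and full protocol are not shown. Data collection says details of all colorectal cancer patients enter the list. If the full protocol has staff record the assumed background for participants too, the problem is largely solved. As written, however, that item sits in the paragraph on non-participants. A statistical analysis plan cannot later recover a field that was never collected.

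Four stronger readings are tempting, and the documents do not support them.

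- *The check is biased towards showing good migrant participation.* This needs Sp close to 1. Missed second-generation patients make under-recognition plausible, but Se 0.9 with Sp 0.95 reverses the direction and Se 0.9 with Sp 0.98 nearly cancels it. The article gives a median age at diagnosis of 71 years for men and 75 for women, and says many first-generation migrants are now reaching that age. The group hardest to recognise may therefore be a minority.
- *This is the only check on selection.* Age, gender, stage and refusal because of language are also recorded for non-participants. Process evaluation follows participation by centre, and Data quality assurance tracks the number of migrants and the stage distribution.
- *The non-participants' stage data are useless for correction.* The article promises only to assess and describe selection, and analyses over a range of error rates remain possible.
- *Ineligible patients contaminate the comparison.* Consent is an inclusion criterion, but the screening list assesses the criteria for each patient, so eligible decliners can be separated out.

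**Conclusion.** The point holds for comparisons that use the migration status of non-participants. There, measuring method and participation coincide, and the article's assurance that selection can be assessed from the screening list is not met. The error can run either way: for a true share of 15.6%, the displayed share is 9.4% to 14.0% with Se 0.6 to 0.9 and Sp 1, and 18.3% with Se 0.9 and Sp 0.95. These error rates are illustrative, and 15.6% describes older Frankfurt residents rather than screened patients. The actual direction and size cannot be determined from the article.

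A reader might infer that the main result is itself misclassified. It is not: the migrant versus non-migrant stage analysis uses questionnaire data from participants. For age, gender and overall stage, the article describes no comparable difference in source. The article's own example, higher participation of patients with low-stage disease, can therefore still be checked overall, though not reliably within migrants and non-migrants. What is weakened is the evidence that the analysed sample is not selected by migration status and stage jointly.

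**What to change.** 1. In Data collection, have staff record the assumed migration background and country of origin for every screened patient with colorectal cancer, before the questionnaire is seen.
2. In Analysis, compare participants with eligible non-participants on this common measure. Keep the questionnaire definition for the main analysis.
3. Among participants, report the agreement between the staff assumption and the questionnaire, with Se and Sp.
4. Use these in a sensitivity analysis of stage by migration status in all eligible screened patients. Show it over a range of Se and Sp, because values from participants may not carry over to non-participants; staff may, for instance, recognise those who decline over language more easily.

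The cost is one extra screening-list field per participant and one extra analysis. The sample size and the main analysis do not change. If the field cannot be added, the article should say that participation by migration status, and stage by migration status among non-participants, rest on an unvalidated staff assumption.
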